#### Reporting of SAEs

All side effects collected as outcomes in the CRF that also meet the definition of serious will need to be reported as an SAE during the trial’s safety reporting window. The safety reporting window is from the day of surgery (intervention) until the 90 day postoperative outpatient review at the end of the trial. Reporting must be within 24 hours of the site being aware of the SAE. Once a SAE is entered in the RedCap trial database, this automatically triggers a notification to the clinical trial unit.

##### Follow-up of SAEs

A follow-up report must be completed when the SAE resolves, when it is unlikely to change or when additional information becomes available. Follow-up information must also be provided as requested by the trial office.

### Monitoring and data safety monitoring board

Regular central monitoring will be performed by the clinical trials unit, according to the trial specific monitoring plan. Following written standard operating procedures, the monitors will verify that the clinical trial is conducted and data are generated, documented and reported in compliance with the protocol, good clinical practice (GCP) and the applicable regulatory requirements. Monthly trial management group meetings will be held to review the conduct and progress of the trial, assess safety and efficacy of the trial interventions and monitor safety of the participants. A trial steering committee will act as an independent body responsible for the overall supervision of the study on behalf of the trial sponsor. The trial steering committee will assess patient safety, conduct of the trial according to principles of GCP and the UK Clinical Trial Regulations. Meetings will take place at 6-month intervals.

### Participant timeline

Please refer to figure 2 for the trial schedule of procedures.

## Statistical considerations

### Sample size

The aim of this trial is to assess the feasibility of an RCT in no-mesh implant-based pre-pectoral breast reconstructive surgery. Therefore, to achieve this aim, the sample size is based on estimating the feasibility outcomes with the desired precision and not hypothesis testing.

Results will be reported in line with the CONSORT guidance on reporting randomised feasibility trials. No formal statistical comparison between groups is planned given the nature of the trial. The main focus of the statistical analysis is on quantifying uncertainty related to the feasibility measures: proportion eligible, consenting, randomised with data and follow-up data available. The overall implant loss, implant infection and seroma rate will be calculated to add related sample size calculations for a definitive trial. 95% CI for feasibility measure will be calculated using appropriate methods (eg, Wilson’s for binary). All outcomes will be summarised using descriptive summary statistics overall and, when collected for both arms, by treatment groups. Binary and categorical data will be summarised by frequencies and percentages. Continuous data will be summarised by means and SDs or median and IQR range if data are skewed. Visual representation of outcomes will be considered and, where it will support interpretation, presented.

The number of eligible participants in total, the number of participants that consented for inclusion, and the number of eligible participants randomised will be reported descriptively. Primary feasibility outcomes will be assessed with follow-up rates at each time point also reported.

### Recruitment

A proposed recruitment target of 40 patients across four centres is estimated according to reconstruction rates in each centre, previous surgical trial experience on recruitment rates (20%) and to allow a 10% withdrawal rate. The actual recruitment rate is unknown and part of the feasibility outcome data to be collected in this trial. Each centre will recruit for a total of 12 months to enable an estimation of actual recruitment rate for this trial. Recruitment data at 6 months will be assessed to determine if further sites are required to facilitate recruitment numbers. Recruitment commenced on the 19 March 2024 and will cease on the 31 August 2025.

### Randomisation

Randomisation will take place once informed consent has been given, eligibility has been confirmed and baseline questionnaires have been completed. The randomisation schedule will be designed by the chief trial statistician who will hold the allocation code. Randomisation will use a 1:1 ratio, via a secure web-based system developed and maintained by the Oxford Surgical Intervention Trials Unit in accordance with standard operating procedures. Stratification by centre will help to ensure that any centre effect will be equally distributed in the trial arms and enable practical issues associated with the active intervention to be overcome. This will be the only stratification factor. In the case of bilateral operations, the participant will be randomised, not each breast. The web-based system is accessed by the surgeon via RedCap. Randomisation allocation will be revealed to the surgeon online, and this will be accessed while the patient is in the anaesthetic room preparing for surgery. Selection bias at the point of recruitment will be minimised using strict inclusion criteria.

### Blinding

Due to the nature of the intervention, it is not possible to blind the surgeons for the purpose of the trial. Participants will be blinded to their allocation. On withdrawal or at the end of the trial, the patient will be informed of their allocation at 90 days postoperatively. Unblinding will occur after completion of the 90 day postoperative QoL questionnaire to reduce bias in its completion. Data will be collected on the administrative processes of randomisation, allocation concealment and the effectiveness of the blinding strategy of the patient to the allocation. Assessment of cosmesis between the two arms will be via a blinded panel of surgeons and patient public representatives using an established cosmetic scoring system.^11^ All questionnaires used in the trial (EQ5D and BREAST-Q) are validated questionnaires. Trial data analysis will be blinded to allocation to reduce bias in data interpretation.

### Data management

Participant data will be handled according to the central clinical trial unit’s standardised procedures, within the University of Oxford and will be compliant with all GDPR (General Data Protection Regulation) requirements.

### Statistical methods

#### Primary analysis

One key objective is to ascertain the recruitment rate of a definitive trial. Based on the four sites’ current reconstructive rates over a 12-month recruitment period, it is expected that there will be 15 eligible patients per month or 180 in total. Observing 180 patients allows the recruitment rate to estimate with a 95% CI width (Wilson’s method) of 9–15% depending on the event rate. Allowing for a recruitment rate of 25% of eligible patients, three to four per month, over 12 months, our sample size will be 40 patients to be recruited (20 per arm). The eligibility and recruitment rates observed in the feasibility trial will determine how many centres are required for feasible recruitment into the main trial within a reasonable timeframe.

The optimum primary endpoint for the main trial will be determined by both the variability and the completeness seen in this feasibility trial and will be decided through patient and professional qualitative interviewing and stakeholder surveys. Important long-term clinical outcomes will also be assessed within the main trial, including implant migration, mesh erosion, capsular contracture and surgery revision rates at 12 months post operation from patient records. The subsequent sample size calculation, along with the eligibility and recruitment rates observed in the feasibility trial, will guide how many centres are required for feasible recruitment into the main trial within a reasonable timeframe.

#### Secondary analyses

Qualitative interviewing: participant qualitative interviews as deidentified transcripts will be analysed using thematic analysis guided by a modified grounded iterative theory approach, allowing early interviews to enrich data collection in later interviews. Participants will be interviewed until analytic categories are richly covered with no further emergent themes. Three levels of coding will be used to develop conceptual analysis to identify barriers to participation in research and patient understanding of mesh in breast reconstruction. The data will be analysed using both a systematic and mind-mapping approach.^12^Breast biomechanics: data from the breast biomechanics substudy are anonymous and analysed to determine differences between breast three-dimensional motion preoperatively and postoperatively between the two interventions.Economic analysis: data from patient diaries, patient ranking of outcomes and results from the QoL questionnaires will inform the development of a decision model structure to represent the natural history of patients in IBBR. An early evaluation of the model using data from the feasibility study will help to inform cost-effectiveness analysis between the two trial interventions.

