**Methods and analysis:**

UK-based pragmatic multicentre randomised controlled feasibility trial. The primary aim is to determine the feasibility of a definitive RCT comparing the clinical and cost-effectiveness of no-mesh versus mesh-assisted prepectoral breast reconstruction. Secondary objectives will explore patient understanding of mesh and willingness to be randomised within an RCT; determine if it is possible to collect data to inform a future economic analysis on the use of mesh in breast reconstruction and determine the feasibility of measuring breast biomechanics pre-surgery and post breast reconstruction surgery. Total number of patients to be included: 40 (20 per arm).

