**Trial registration numbers:**

NCT06112977; ISRCTN17470747.

STRENGTHS AND LIMITATIONS OF THIS STUDYThis is a pragmatic well-designed feasibility randomised controlled trial (RCT) which aims to determine if a future RCT is possible to run to determine the role of mesh in breast reconstruction.A mixed-methods qualitative and quantitative approach with patient public involvement input throughout the trial processes has been designed to understand all stakeholders’ views. Importantly, participant views on the acceptability of blinding and surgeon views on randomisation will be collected as these may be key barriers to future trial recruitment.The data from a feasibility RCT may support the safety and acceptability of the intervention; however, no statistically significant differences can be determined between the two groups of data.The study is limited to short-term surgical outcomes, and longer-term surgical and oncological outcome measures will be collected pending further ethical approval and funding.

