### Data collection methods

Intraoperative data will be collected including details on the mastectomy technique and volume, the type and volume of prosthesis (±mesh) used in the operation, mastectomy weight, use of sutures, drains and antibiotics.

Preoperative, perioperative and postoperative care will be standard NHS care as per local practice including standard surgical outpatient follow-up at 14 days, 30 days and 90 days. Clinical outcome data will be collected at the same time points as NHS care. Clinical data collected includes clinical history, clinical postoperative complications and patient access to healthcare outside of the tertiary hospital setting via patient weekly online diaries.

Patients will be contacted at 90 days to complete an online (or paper) QoL post-operative questionnaire (in rare cases by telephone). Following completion of the 90-day QoL questionnaire, the patient will be unblinded to their allocation. Standard postoperative oncoplastic photographs will be collected at 90 days to assess breast aesthetics. Patients can report complications or additional healthcare visits to the research team via their weekly online diary. Serious adverse events will be recorded and reported if unexpected and related. Feasibility outcome data will be collected alongside clinical outcome data. Data will be collected from participants via questionnaires and CRFs. Paper questionnaires (where used) will be returned to the central trial office in Oxford via post using a preaddressed freepost envelope. Electronic questionnaires will feed directly into an online secure database—the study’s dedicated instance of REDCap (figure 2 shows the schedule of events).

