####  Optional

Patients, when offered participation in the trial, will be in parallel offered to participate in the substudy looking to identify patient views on mesh in breast reconstruction, the design of the trial and barriers to participation in research. A patient information sheet and consent form for the qualitative interview (previously approved ethics reference: Narratives of health experience insights for https://hexi.ox.ac.uk and www.youthhealthtalk.org. b NRES Committee South Central - Berkshire 122/SC/0495. IRAS ID 112111). This is in the form of a 1-hour virtual (or face-to-face) qualitative interview with the trial research team. Patients can participate in this study regardless of their decision to take part in the main study. Participants in this substudy will be compensated for their time with a gift voucher. Deidentified transcripts will be analysed using thematic analysis, guided by a modified grounded iterative theory approach, allowing early interviews to enrich data collection in later interviews. Patients will be interviewed until analytic categories are richly covered with no further emergent themes. Three levels of coding will be used to develop conceptual analysis.Patients who decide to consent to participate in the main trial will be offered the opportunity to take part in the substudy determining the feasibility of collecting breast biomechanic data presurgery and post breast reconstruction surgery. Patients will be approached preoperatively in the outpatient setting by the consenting surgeon. Trial information and trial consent for biomechanics will be supplied to patients at this visit. Participants who wish to participate will be invited to attend a preoperative and postoperative visit (at 90 days) to the biomechanics laboratory for data collection in addition to their standard NHS care visits to their hospital. Patients will need to be able to travel to the biomechanics data collection site at the University of Portsmouth. Patients will be compensated for their travel costs to the biomechanics laboratory. Participants who do consent to biomechanical data collection will have an appointment made at the University of Portsmouth breast biomechanics centre. Electronic sticker sensors (Liberty MicroSensor, Polhemus, Vermont, USA; CE Marked) will be placed onto the patient’s chest wall and breast and the patient will be asked to stand, walk slowly and walk quickly with the sensors collecting data on breast volume, shape and position statically, plus full body and breast kinematics dynamically, as well as perceptual feedback related to their breasts. Breast volume, shape and position will also be assessed statically using 3D scanning (Artec Eva 3D, Luxembourg; CE Marked). Three-dimensional motion of the body and breast will be tracked using electromagnetic sensors and data derived to calculate breast motion relative to the torso (six df). All biometric data collected is anonymous and linked to the participant study ID. Biomechanical data will be analysed by the research team. Participants in this substudy will be offered an optional questionnaire to record their views on this aspect of the trial. All participants will be given a complimentary bespoke postoperative bra according to their breast biomechanical data.

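### The biomechanics substudy has a feasibility objective but a stated aim of finding differences between arms, and its perceptual ratings can fall after unblinding

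*Protocol article*

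**What the plan says.** **Objective.** The abstract sets a secondary objective to "determine the feasibility of measuring breast biomechanics pre-surgery and post breast reconstruction surgery". The Objectives section repeats a feasibility aim for the substudy.

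**Analysis.** The only analysis that the article states for the substudy is in Secondary analyses: the data are "analysed to determine differences between breast three-dimensional motion preoperatively and postoperatively between the two interventions".

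**Rule for the trial as a whole.** The Sample size section states: "No formal statistical comparison between groups is planned given the nature of the trial". It adds that "the sample size is based on estimating the feasibility outcomes with the desired precision and not hypothesis testing", and that outcomes are summarised descriptively, overall and by arm. The strengths and limitations box concedes that "no statistically significant differences can be determined between the two groups of data".

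**Who takes part.** The Optional part of Data collection methods offers the substudy to consenting main-trial participants, who are approached before surgery and must be able to reach one laboratory. No substudy sample size is given. The main trial has 40 patients, 20 per arm.

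**Timing.** The same part places the postoperative laboratory visit at 90 days, in addition to the usual hospital visits, and lists among the data collected sensor-measured motion, "as well as perceptual feedback related to their breasts". On unblinding, Data collection methods says: "Following completion of the 90-day QoL questionnaire, the patient will be unblinded to their allocation". Trial design and setting and the Blinding section use the same trigger. The Blinding section explains it as protection for that questionnaire.

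**The concern.** There are two separate issues.

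1. **Aim.** An analysis that sets out to find differences between the two techniques does not answer whether breast motion can be measured before and after surgery in trial participants. An analyst who followed Secondary analyses literally could produce a mesh versus no-mesh claim about motion from very few women, although the rest of the plan says that the trial cannot support such claims.

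2. **Blinding.** The trial is participant-blinded, and the order of events at 90 days is arranged to protect one participant-reported measure. A second such measure, the perceptual feedback at the laboratory, is not covered by that arrangement. The questionnaire is usually completed online and the laboratory visit is a separate trip, so the questionnaire could well come first. The rating would then be open to expectation bias.

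**Working it through.** **Step 1: the plan's own figures.** The Primary analysis section expects 180 eligible patients and a 25% recruitment rate; the Recruitment section gives 20% recruitment and 10% withdrawal.

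- 180 × 0.25 = 45, and 45 × 0.9 = 40.5.
- 180 × 0.20 = 36, and 36 / 0.9 = 40.
- Wilson 95% interval width for n = 180: 8.83 points at a rate of 10%, 12.56 at 25%, 14.46 at 50%. This agrees with the stated 9–15% for rates of about 10% to 50%.

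The total of 40 and the stated precision therefore reproduce. No stated figure is wrong, and none of them concerns biomechanics.

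**Step 2: what a between-arm comparison could show.** The plan gives no SD, effect size or uptake for the substudy, so the following is an illustration. Assume a two-sample t comparison of pre-to-post change, two-sided 5%, common SD of change = 1, and n women per arm with both visits.

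- Power: P(T > t(0.975; 2n − 2)), with T noncentral t on 2n − 2 degrees of freedom and noncentrality d × √(n/2).
- Detectable difference: the d at which that power is 0.80.
- 95% CI half-width: t(0.975; 2n − 2) × √(2/n).

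For n = 10 the half-width is 2.101 × √0.2 = 0.94 SD.

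| n per arm (assumed) | Power at 0.5 SD | Power at 0.8 SD | Difference for 80% power | CI half-width |
|---|---|---|---|---|
| 20 (all join) | 0.338 | 0.693 | 0.91 SD | 0.64 SD |
| 18 (all join, 10% lost) | 0.308 | 0.645 | 0.96 SD | 0.68 SD |
| 10 | 0.184 | 0.395 | 1.32 SD | 0.94 SD |
| 5 | 0.104 | 0.200 | 2.02 SD | 1.46 SD |

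By the normal approximation, 80% power needs 63 per arm at 0.5 SD and 25 per arm at 0.8 SD. Both exceed the whole trial.

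**Step 3: what the substudy can report.** Take an assumed uptake of 20 out of 40. Wilson width = 2 × 1.96 / (1 + 3.8416/40) × √(0.25/40 + 3.8416/(4 × 1600)) = 3.5765 × 0.0828 = 0.296, so the interval runs from about 35% to 65%. This is wide, but it answers the stated objective.

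**Step 4: does opting in break the randomised comparison?** Women are approached for the substudy before surgery and have a preoperative laboratory visit. Under Randomisation, the allocation is shown to the surgeon only when the patient is in the anaesthetic room. Entry therefore comes before anyone treating the patient sees the allocation. Selection by willingness and travel limits precision and generalisability but does not itself unbalance the arms.

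**Step 5: order of events at 90 days.**

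- Questionnaire: 90 days, online, on paper or rarely by telephone. Its completion triggers unblinding.
- Laboratory visit: 90 days, a separate appointment. Perceptual feedback is taken there.
- Rule linking the two: none in the text shown.

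Both orders are thus allowed. If the questionnaire comes first, the perceptual rating can be given unblinded. The motion data come from sensors and are much less exposed.

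**The case against.** The strongest reply is that nothing formal is planned. The Sample size section excludes only formal comparison and prescribes descriptive summaries by arm. Secondary analyses names no test, model or hypothesis, so the two can be read together as a descriptive look at motion by arm. This stands. A reader might infer that the plan schedules an inferential test against its own rule, and the text does not support that. What remains is that the stated aim is comparative where the objective is feasibility, and nothing in the sentence marks it as descriptive.

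It follows that the detectable differences test something nobody has planned. This is also right: they show why the aim is out of reach, and do not reveal a miscalculation.

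A reader might also infer that a self-selected subset is no longer a randomised comparison. Step 4 shows why this does not follow. Unequal failure to return for the second visit could cause imbalance, but nothing in the document points to it.

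On blinding, two limits hold. First, the order of questionnaire and laboratory visit may be fixed in the flow chart, the schedule figure or the full protocol, none of which is shown, so it cannot be said that women will be unblinded first. Second, the motion analysis does not include the perceptual feedback, for which the article describes no between-arm analysis. It would be wrong to infer that the motion comparison is biased by unblinding.

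Finally, an article may leave the list of substudy feasibility measures to the full documents. Their absence is not held against the plan here; the point is that the analysis it does state has a different aim.

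**Conclusion.** The point holds as two modest corrections to a secondary, optional substudy.

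- **Aim.** The stated analysis does not match the stated objective and reads against the trial's own position on comparing arms. Even with full uptake, only a difference of about 0.91 SD would have 80% power; with the assumed 10 or 5 per arm it is 1.32 or 2.02 SD. These figures rest on assumed uptake, a common SD and a two-sided 5% t comparison.
- **Blinding.** The visible text allows perceptual ratings after unblinding. How often this would happen cannot be estimated from the document.

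The progression decision for the main trial is not shown to be affected.

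**What to change.** **Secondary analyses.** Reword the biomechanics item to match the objective. Report the proportion consenting to the substudy, the proportion attending both visits and the proportion with usable sensor and scan data, each with a Wilson interval, the method already named in the Sample size section. Present pre-to-post change in motion by arm as descriptive estimates (mean and SD) for planning only, with no between-arm inference.

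**Unblinding.** In Trial design and setting, Data collection methods and Blinding, set disclosure after the last participant-reported 90-day assessment, including the laboratory visit for those who consented to it. A lighter alternative is to require that perceptual ratings are taken before disclosure and to record blinding status at the visit. That fits the existing plan to collect data on how well blinding worked. If the schedule or full protocol already fixes the order, one sentence saying so is enough.

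**Cost.** The first change is wording. The second delays disclosure slightly for substudy participants and, because it alters when they learn their allocation, needs approval as a protocol amendment. Neither changes the sample size.
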